### Interventions

The treatment phase starts after the participant is deemed eligible and agreed to participate voluntarily and signed a structured consent form. After randomization, participants will be allocated to one of two groups described below. The treatment phase will last 5 weeks.

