### Experimental group (EG)

#### Exercise programme

The list of exercises to be conducted in all therapeutic sessions (Additional file 1) was constructed based on previous studies and following recommendations commonly reported in the literature [26, 29–31].Two to three sets of 10 to 15 repetitions will be performed using elastic therapeutic bands and dumbells. Three repetitions of 15 s of the stretching exercises will be performed after the strengthening exercises. Exercise progression load will be individually based and managed in a way that a value of a maximum pain score of 5/10 on a verbal rating scale (0 - no pain and 10 - maximal tolerable pain) should be observed during the execution of the exercises. If no such symptom occurs, a score of 6 on a BORG scale (0 – rest and 10 – extremely strong) will be applied. Therefore, during the treatment sessions, the load utilized (dumbells or elastic bands) will be adjusted according to the perception of symptoms. On the first session, 2 sets of 10 repetitions respecting the aforementioned symptoms will be conducted. In this way, participants will become familiar with the exercise programme and this will also inform on immediate symptom reproduction after the session. On the second session, 3 sets of 10 repetitions will be performed. Then, every week after that, 3 sets of 15 repetitions will be conducted with the adjusted load (same load, more load or less load) based on the perception of symptoms. An interval of 45–60 s will be provided between sets and exercises. Participants will be informed about the importance of increasing the load, while still respecting symptoms. In addition, if symptoms provoked by the exercise programme are still present 24 h later, the exercise load will be diminished until this no longer occurs.

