### Participant timeline

The enrollment process will begin from the end of February 2020. After entering the study, participants will have the following outcomes assessed at baseline: SPADI, NPRS, AROM, PPT, expectations and SE; at the end of the treatment period: SPADI, NPRS, AROM, PPT and GROC; and at one month follow-up: SPADI, NPRS, and GROC. Expectation is the only outcome measure to be collected during the third week of treatment. Figure 2 depicts enrolment, interventions and assesssments timeframes throughout the study. Participants will attend ten individual sessions, twice a week (approximately 40 min each), in either of the available treatment sites, according to their geographic locations (see study settings). For the follow-up, participants will be contacted by a research member via email or mail to fill out the respective outcome measures. A telephone call will be made for participants that miss one treatment session without providing explanations.

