### Harms

Due to the nature of this study, we understand that it is important to control for adverse events that might occur as a result of the procedures applied. In order to monitor these, this study will use an adapted questionnaire [52], were participants will respond to the following question: “Have you experienced any discomfort or unpleasent sensation as a result of this treatment?”. Participants will inform (discomfort, soreness, fatigue, etc), rate their sensation using the NPRS (0–10, 10 meaning highest value) and inform when it started (< 30 min after treatment, between 30 min - 4 h, etc) and if it has affected their home or work activities (nothing, little or much). This scale will be applied at each treatment session.

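### The harms form is scheduled only at treatment sessions, so delayed reactions after the tenth session and events up to the one-month follow-up have no stated harms-form contact

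*Protocol article*

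**What the plan says.** The Harms section describes an adapted questionnaire built on one question, "Have you experienced any discomfort or unpleasent sensation as a result of this treatment". Participants name the sensation, rate it from 0 to 10, state how far it affected home or work, and "inform when it started (< 30 min after treatment, between 30 min - 4 h, etc". The timing is then fixed: "This scale will be applied at each treatment session". No other time point for harms appears in the article.

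On exposure, the Interventions section states that "The treatment phase will last 5 weeks", and the Participant timeline that "Participants will attend ten individual sessions, twice a week (approximately 40 min each".

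The Participant timeline also lists what is collected later. At the end of treatment the list is SPADI, NPRS, AROM, PPT and GROC. The last collection is "at one month follow-up: SPADI, NPRS, and GROC", obtained by email or mail. Neither list has a harms item. For absences, the same section says: "A telephone call will be made for participants that miss one treatment session without providing explanations". It does not say what is asked on that call. The Statistical analysis section adds that drop-outs will be reported with their reasons.

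**The concern.** The form and its schedule do not fit together. The form is designed to capture reactions that begin after the participant has left, since one of its bands runs from half an hour to four hours after treatment. Such a reaction can be recorded only when the participant is next asked. If the form is given only at sessions, each session in effect collects the delayed reactions to the session before it, and nothing collects those to the last session. The same holds for anything that emerges between the end of treatment and the one-month follow-up.

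A related weakness concerns participants who stop coming. The form depends on attendance, so someone who leaves after a reaction is not asked its questions on intensity, onset and interference unless another contact is used for that purpose, and none is stated.

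The stake is the harms report, not the efficacy estimates. The Harms section treats the monitoring of adverse events as important, and the Discussion says the trial should help clinicians decide whether to add MWM to exercise. How well MWM is tolerated relative to sham is part of that decision, and a reaction not asked about during the trial cannot be reliably recovered at analysis.

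**Working it through.** The article gives no harms figure to reproduce. The check sets the harms schedule against the visit schedule.

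**Inputs**
- Sessions per participant: 10, two per week (Participant timeline). Consistent with Interventions: 5 weeks × 2 per week = 10.
- Participants: 70 (Sample size).
- Harms form: at sessions only (Harms).
- Onset bands: include 30 minutes to 4 hours after treatment (Harms).
- Treatment period: 5 weeks = 35 days (Interventions).
- Follow-up: one month (Trial design), taken here as 28 to 30 days. This is an assumption.

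**Step 1: delayed windows.** A delayed reaction to session *k* can be reported at session *k* + 1. For *k* = 1 to 9 such a session exists; for *k* = 10 it does not.
- Windows followed by a session: 9/10 = 90%.
- Windows not followed by a session: 1/10 = 10%.

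**Step 2: trial total if everyone attends every session.**
- Delayed windows: 70 × 10 = 700.
- Windows with no later session: 70 × 1 = 70.
- Share: 70/700 = 10%.

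This is an upper figure for full attendance, and it counts windows for delayed onset only. A reaction during session 10, or before the participant leaves, can still be recorded that day.

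**Step 3: time without a scheduled harms question.** Share = follow-up days / (treatment days + follow-up days).
- 28-day month: 28/(35 + 28) = 28/63 = 44%.
- 30-day month: 30/(35 + 30) = 30/65 = 46%.

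**Step 4: could another contact fill the gap?**

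| Contact | What the article says is collected | Harms form stated? |
|---|---|---|
| Each treatment session | Harms questionnaire | Yes |
| End-of-treatment assessment | SPADI, NPRS, AROM, PPT, GROC | No |
| One-month email or mail | SPADI, NPRS, GROC | No |
| Call after an unexplained missed session | Not specified | No |

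NPRS and GROC can show that a participant is worse. They do not attribute the worsening to treatment, date it, or record its effect on home or work, which is what the harms form is for.

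**The case against.** Several points on the other side have force.

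**The assessment lists are incomplete.** The Participant timeline omits self-efficacy after baseline, although the Self-efficacy section schedules it at the end of treatment and at follow-up. The body of Figure 2 is not available. The absence of harms from those lists is therefore weak evidence by itself. That stands, but the point rests on the Harms section, which states its own timing, and no other section adds to it.

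**Drop-outs are not invisible.** A reader might infer that reactions leading to withdrawal are never counted. The article does not support this: the missed-session call and the reporting of drop-out reasons give such reactions a route into the record. The route is partial, because the call applies only to unexplained absences and is not said to include the form.

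**The size among drop-outs cannot be calculated.** It is tempting to treat the 20% loss allowance as withdrawals during treatment. The Sample size section calls it loss to follow-up, which may include unreturned one-month forms, and nothing says when losses occur.

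**The direction of bias is not established.** For completers the gap is the same in both arms, and both receive the same exercise programme. The worse-tolerated arm would look safer only if reactions caused more withdrawals in one arm than the other. That is possible but is not shown. Harms are not listed as a primary or secondary outcome, so no planned efficacy comparison is affected.

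**The form is only summarised.** The Exercise programme section provides that "if symptoms provoked by the exercise programme are still present 24 h later, the exercise load will be diminished until this no longer occurs". A reader might infer that the harms form is wrong to lack a duration item. But the article condenses an adapted instrument, and nothing says this instruction was meant to be traceable in the harms data. There is no error to claim.

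**No treatment session is described in the follow-up month.** Asking about harms then is less pressing than covering session 10. It still costs little, since the participant is being contacted anyway.

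**Conclusion.** The point holds as a limited gap in the stated schedule. Followed as written, delayed reactions after the tenth session (1 of 10 delayed windows; up to 70 of 700 with full attendance) have no stated harms-form contact. Nor do events in the month to follow-up, about 44% to 46% of the observation period if that month is 28 to 30 days. For participants who stop attending, reactions are not systematically collected with the form, though some may come to light by other routes.

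The conclusion assumes that the harms form is used only when the Harms section says it is. It does not depend on how many participants withdraw or when. It does not mean that the whole of the last exposure goes unobserved, because immediate reactions at session 10 can be recorded that day. Nor does it affect the primary analyses or the sample size. It is worth changing because the correction is cheap and uses contacts already planned.

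**What to change.** Amend the Harms section and the Participant timeline so that the same questionnaire is used as follows:

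1. At each treatment session, as now, with the question worded to cover the interval since the previous session.
2. At the end-of-treatment assessment, to cover the tenth session.
3. In the one-month email or mail package, to cover the period since the end of treatment.
4. On the call after a missed session, and at any withdrawal contact.

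State that harms will be reported by allocated arm from first session to follow-up, including withdrawals due to a reaction.

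The cost is small: the same short form at contacts that already take place, a few more minutes per participant, and possibly a higher reported harm count. No new visits are needed, and randomisation, primary outcomes and sample size are unchanged.

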### Research ethics approval, consent & confidentially

Ethical approval for this study was obtained from *Universidade Federal de Ciências da Saúde de Porto Alegre* Ethics Commitee (number 3.528.946) and the trial is registered at ClinicalTrials.gov with the identifier NCT04175184. Table 2 provides information regarding registration data set. Subjects will provide informed consent prior to participation in the trial. Participants personal data and their research data will be kept confidential and will not be disclosed to any other party not participating in the study.

**Table 2 Tab2:** Trial registration data set

Category	Information
Primary registry and trial identifying number	ClinicalTrials.gov NCT 04175184
Date of registration in primary registry	November, 2019
Ethics Committee number	UFCSPA Ethics Committee CAEE: 3.528.946
Source(s) of monetary or material support	Self-funded
Contact for public queries	[name], [contact]
Contact for scientific queries	[name], [contact]
Public title	The use of MWM and exercises in shoulder pain.
Scientific title	The inclusion of Mobilisation with Movement to a standard exercise programme for patients with rotator cuff related pain a randomised, placebo-controlled protocol trial.
Countries of recruitment	Brazil
Health condition and problem studied	Shoulder pain related to rotator cuff
Intervention	Mobilisation with movement
Comparator	Sham mobilisation with movement
Key inclusion and exclusion criteria	Age: 18–65 years;Inclusion criteria: ≥6 weeks shoulder pain of atraumatic origin; pain on movement. Exclusion criteria: specific shoulder conditions (fracture, dislocation, arthritis, adhesive capsulitis, cancer, previous surgery, radicular signs).
Study type	Interventional Allocation: randomised; sham-controlled clinical trial with parallel groups; double-blind.
Date of first enrolment	March, 2020
Target sample size	70
Recruitment status	Recruiting
Primary outcome(s)	Function and pain
Key secondary outcome(s)	Active range of motion, pain pressure threshold, global perceived effect, self-efficacy and expectations.

## Discussion

The current evidence for the conservative management of RCRP suggests that exercise with or without manual therapy should be considered. However, despite being recognized as a manual therapy approach, MWM differs from many other manual therapy procedures as it involves active movement on the part of the patient combined with a passive manual therapy procedure. Usually, the active movement chosen is the specific impairment identified as the patient’s main problem. This aspect is particularly important in patients with RCRP as painful and / or restricted movement is commonly encountered on physical examination and subjectively reported as a chief complaint.

Previous studies have found contradictory findings when comparing MWM to sham MWM [18, 19, 21]. The differences in the results observed might be due to methodological aspects (participants´ clinical profile, dosage, type and expertise of the MWM used, follow-up and outcome measures). However, none of the above studies have applied MWM pragmatically. This is considered a critical aspect of the use of MWM. Often in clinical practice, there is a need to change aspects related to the MWM procedure such as: force and direction of the glide, position of the patient, location where the MWM is applied and load used. Therefore, this clinical trial will assist in verifying whether these pragmatic aspects produce better results.

Another key point not sufficiently explored in previous studies is the incorporation of MWM together with exercise in the management of patients with RCRP, reflecting common clinical practice. Only one pilot study has investigated the use of MWM with exercise [22]. However, the age group (83.9 +/− 8.2 years) and clinical settings (nursing home) differs from the current study.

Taking into consideration the high prevalence of RCRP and limited spectrum of studies investigating MWM with exercises, there is a need to verify the impact of adding MWM to an exercise programme in this population. A study comparing different treatment options, that is sham-controlled, will help inform healthcare professionals in the decision making process related to the inclusion or not of MWM in patients with RCRP.

## Data Availability

Not yet applicable as the study has not started. However, future data will be available from the corresponding author on reasonable request.

## Abbreviations

ANCOVA: Analysis of covariance
ANOVA: Analysis of variance
AROM: Active range of motion
CONSORT: Consolidated standards of reporting trials
CG: Control group
EG: Experimental group
GROC: Global rating scale of change
MWM: Mobilisation with movement
NPRS: Numeric pain rating scale
PPT: Pain pressure threshold
RCRP: Rotator cuff related pain
SE: Self-efficacy
SPADI: Shoulder pain disability index
SPIRIT: Standard protocol items for randomised interventional trials
SPSS: Statistical package for social Science
